### 2.10. Statistical Analysis

The principal analysis will be conducted on a full analysis set (FAS), which consists of participants randomly allocated into two groups. Participants completing and complying well with the study protocol without major violation will be referred to the per-protocol population. All participants taking test drugs will be enrolled in safety analysis and conform with the ITT principle.

For non-normally distributed variables, mean ± standard deviation or median will be brought to describe continuous variables. Categorical variables will be presented in the form of numbers and percentages. The difference in Scr will be tested using the one-way ANOVA with repeated measures. The secondary outcomes will be compared between two groups using the independent-samples Student's *t*-tests for normally distributed continuous data and using Pearson's chi-square test (or Fisher's exact test if cell count <5 in any cell) for categorical data. Two-sided tests will be used for all statistical tests, and *P* < 0.05 will be considered statistically significant. SPSS (version 21.0) software will be used to carry out statistical analysis by a biostatistician not involved in the study. No additional analyses or interim analysis will be performed.

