**Methods:**

This is a multicenter randomized controlled clinical trial. We intend to enroll 162 participants, and these participants will be divided into the RG group, the CHF group, and the RG + CHF group randomly assigning 1 : 1 : 1 principle. The RG group will be general treatments combining RG, the CHF group will be general treatments combining CHF, and the RG + CHF group will be general treatments combining RG and CHF. The duration of treatment will last two weeks. The primary evaluation outcome will be the change in the slope of serum creatinine (Scr) over 2 weeks. Secondary evaluation outcomes include changes in blood urea nitrogen (BUN), estimated glomerular filtration rate (eGFR), urinary AKI biomarkers (neutrophil gelatinase-associated lipocalin (NGAL), interleukin-18 (IL-18), gamma-glutamyl transpeptidase (*γ*-GT), etc.), traditional Chinese medicine (TCM) symptoms, inflammatory indicators, and oxidative stress indicators. Meanwhile, the vital sign indicators and adverse events (AEs) will be closely observed. These dates will be meticulously recorded and properly handled by investigators throughout the study. *Discussion*. This study will provide convictive research-derived data to evaluate clinical efficacy and safety of CHF combing RG for CKD stages 2–4 complicated with AKI grades 1–2 and provide an evidence-based recommendation for clinicians. The timely completion of this trial will provide a novel drug treatment method for A on C. This trial is registered with ChiCTR2100043311 and registered on February 9, 2021.

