### 2.5. Interventions

Patients diagnosed with CKD stages 2–4 complicated with AKI grades 1–2 will be enrolled after signing written informed consents. They will be randomly divided into the RG group, the CHF group, and the RG + CHF group. To minimize potential loss and help participants conduct the trial smoothly, three group patients will receive study behavior and health education, and they will also be told possible risks and benefits, their rights and obligations, and how to handle an emergency situation. All patients will receive a low-salt, high-quality, and low-protein diet (protein intake 0.6–0.8 g/kg/d). Also, they will receive general treatments, whose purposes are to correct water, electrolyte, and acid-base balance disorders, control blood pressure, improve anemia, and correct renal bone diseases. Designed investigations will keep in touch with participants regularly and assist them to receive treatment and testing on schedule.

The RG group will be given RG 1.8 g added to 0.9% normal saline or 5% glucose 250 ml for injection, intravenous injection (IV), once per day for 2 weeks. The CHF group will be given CHF orally, twice per day for 2 weeks. At the same time, the concentrated solution of CHF will be given an enema, once per day for 5 days, and then rest for 2 days, 5 times in a week. The RG + CHF group will be the combination of the RG group and the CHF group, and intervention methods are the same as the above.

Pharmaceutical compositions of CHF are mainly as follows: prepared rhubarb (Zhida Huang), Ligusticum wallichii (Chuan Xiong), Codonopsis pilosula (Dangshen), Coptidis rhizome (Huanglian), Smilacis glabrae (Tufuling), etc. RG will be produced by Chongqing Yaoyou Pharmaceutical Co. Ltd., and CHF will be produced by Jiangyin Tianjiang Pharmaceutical Co. Ltd. Therefore, the quantity and quality of medicine can be effectively guaranteed.

Related examinations will be conducted and collected at baseline, every 1 week during treatment. Patient information will be recorded, and efficacy-related examinations, mechanism-related indicators, safety-related indicators, and drug management will be closely observed. Measured items and time points are listed in Table 3.

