### 2.9. Sample Size Estimation

The sample size will be calculated according to the primary outcome of baseline Scr change. Based on previous studies and literature reports [26, 30], the mean value of Scr was 160.39 *μ*mol/l, and the standard deviation was 44.43 *μ*mol/l. We thus hypothesize that Scr for CHF combing RG group would be significantly lower than the other two groups by more than 30 *μ*mol/l. It is calculated using the sample size estimation software PASS (version 15.0.3) to achieve test efficacy 1–*β* = 0.90 and significant difference *α* = 0.05 (one-sided test). Considering 20% drop rate, the estimated sample size for randomization will be 54 cases in each group for a total of 162 cases.

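### Section 2.10 describes two groups in a three-arm trial, and no stated test addresses the hypothesis that the combination is lower than both single-drug arms

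*Protocol article*

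**What the plan says.** - **Design.** The abstract states three arms: "these participants will be divided into the RG group, the CHF group, and the RG + CHF group". Sections 2.4 and 2.5 repeat this, with 1:1:1 allocation. The total is 162, or 54 per arm.
- **Hypothesis.** Section 2.9 expects that Scr in the combination arm "would be significantly lower than the other two groups by more than 30" μmol/l. It plans for 90% power and a 20% drop-out rate.
- **Analysis set.** Section 2.10: "The principal analysis will be conducted on a full analysis set (FAS), which consists of participants randomly allocated into two groups".
- **Primary test.** Section 2.10 assigns Scr to a one-way ANOVA with repeated measures. It names no contrast or follow-up comparison.
- **Secondary tests.** Section 2.10: "The secondary outcomes will be compared between two groups", by t-test for continuous data and by chi-square or Fisher's exact test for categorical data. The two groups are not named.
- **Level.** Every test is two-sided at 0.05. The section closes by excluding any additional or interim analysis.

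**The concern.** Two things in Section 2.10 do not fit the rest of the protocol.

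First, the two-group wording appears twice, once in the definition of the principal analysis set. Three arms give three possible pairs, and the text does not say which pair the secondary tests compare.

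Second, the Section 2.9 hypothesis consists of two directional comparisons: combination against RG, and combination against CHF. An omnibus ANOVA asks only whether the three means differ somewhere. If the planned analysis stops there, a significant result could be reported as support for the combination when only one comparator was beaten, or when the whole signal was a difference between CHF and RG. The clinical question is whether adding one treatment to the other helps, and that needs both contrasts.

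**Working it through.** **Inputs.** From Section 2.9: difference 30 μmol/l, SD 44.43 μmol/l, α = 0.05, power 0.90, drop-out 20%. From the abstract: three equal arms. Means are written in the order RG, CHF, RG + CHF. The ANOVA is read as a between-group F-test with three groups.

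**1. Reproducing the planned size.** The F-test has noncentrality λ = n·Σ(μᵢ − μ̄)²/σ².
- For means (0, 0, −30), μ̄ = −10 and Σ(μᵢ − μ̄)² = 100 + 100 + 400 = 600.
- With n = 43, λ = 43 × 600 / 44.43² = 25,800 / 1,974.0 = 13.07.
- The critical value of F(2, 126) at 0.05 is 3.07, which gives power 90.3%. With n = 42 power is 89.5%, so 43 is the smallest n.
- 43 / (1 − 0.20) = 53.75, rounded up to 54 per arm and 162 in total: an exact match.
- Two-sample t-test calculations do not match. One-sided 0.05 gives 39 evaluable and 49 randomised; two-sided 0.05 gives 48 and 60.

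The sample size therefore fits a three-group omnibus test.

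**2. What that test can tell apart.** Keep 43 per arm and SD 44.43.

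| True means (RG, CHF, RG + CHF) | Combination is better than | Σ(μᵢ − μ̄)² | F-test power |
|---|---|---|---|
| 0, 0, −30 | both | 600 | 90.3% |
| 0, −30, −30 | RG only | 600 | 90.3% |
| 0, −30, 0 | neither | 600 | 90.3% |

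The noncentrality is the same in all three rows, so the F-test cannot separate the hypothesis from its failure. In the third row, simulation gives a significant F-test with neither comparator beaten in about 88% of trials.

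**3. Under the hypothesised effect (0, 0, −30).** Simulated trials with 43 per arm and two-sided 0.05 t-tests:
- F-test significant: about 90%.
- Combination significantly lower than both: about 79%.
- F-test significant but only one comparator beaten: about 12% (11.8% with two-sample variances, 11.3% with the three-arm pooled variance).

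With all 54 per arm, power to beat both is about 89% and F-test power is 95.8%.

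**4. False-positive rates when all three means are equal (43 per arm, unadjusted, per outcome).**

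| Rule | Rate |
|---|---|
| Three-group F-test | 5.0% |
| Any of the three pairs significant | 12.2% |
| Either combination contrast significant, either direction | 9.0–9.1% |
| Combination falsely superior on at least one contrast | 4.6% |
| Combination falsely superior on both contrasts | about 0.5% |

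If one comparator really is worse than the combination and the other is equal to it, the both-must-win rule is still bounded by the level of a single test. That is why it needs no α adjustment.

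**The case against.** The strongest reply is that the two-group phrase is a drafting slip. No other section drops an arm, the sample size matches a three-group F-test exactly, and the primary test is an ANOVA that runs at 5%. Section 2.9 also says the combination should be lower than the other two groups, which most readers will take to mean both. Follow-up contrasts and multiplicity rules are often left to a statistical analysis plan, which is not shown here.

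Much of this stands, and it rules out several stronger readings:

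- A reader might infer that the primary analysis runs at 12% error. It does not. Pairwise t-tests are stated only for secondary outcomes, and 12% applies to one such outcome with all three pairs tested unadjusted. False superiority of the combination on either contrast is 4.6%.
- A reader might multiply secondary and mechanism outcomes by three pairs to get a large count of tests. Section 2.10 does not say that three pairs will be tested.
- A reader might infer that an arm will be left out of the analysis set, or that the protocol has no idea of success. The design sections contradict the first, and Section 2.9 states an aim against both comparators.

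The reply does not remove the contradiction. Section 2.10 states a two-group set, two-group comparisons and one contrast-free primary test, and then excludes additional analyses. That exclusion may be meant only for ancillary analyses, but as printed it leaves the Section 2.9 hypothesis without a test. A separate analysis plan that added the contrasts would have to depart from this text.

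**Conclusion.** The point holds for the internal contradiction and for the missing link between hypothesis and test. The two-group wording is wrong for a three-arm trial. The primary test as stated has about 90% power whether the combination is better than both comparators, one, or neither, and about 12% of trials under the planned effect would be significant with only one comparator beaten. The 9% to 12% error range concerns unadjusted pairwise tests on a single secondary outcome only.

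These figures assume that the ANOVA is a between-group F-test on Scr, that the SD of 44.43 applies to the analysed quantity in each arm, and that the data are normal with equal variances. The 79% figure assumes 43 evaluable per arm; 89% applies if all 54 are analysed. Both are needed because Section 2.3.6 removes withdrawn cases from the efficacy analysis while Section 2.3.7 asks for intention-to-treat.

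**What to change.** In Section 2.10:

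1. Define the full analysis set over the three randomised groups.
2. Add: *The primary contrasts for Scr are RG + CHF versus RG and RG + CHF versus CHF. The combination is declared superior only if both are significant, in favour of the combination, at two-sided 0.05.* No α adjustment is needed.
3. Compare secondary outcomes on the same two contrasts, with 95% confidence intervals, as supportive evidence.
4. Make clear that the exclusion of additional analyses does not cover these contrasts.

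In Section 2.9, describe the 90% as the power of the omnibus test, and give the power to win both contrasts: about 79% with 43 evaluable per arm, about 89% with 54.

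**Cost.** The change is to wording and needs no extra patients. The price is that the power for the claim the trial wants to make falls short of 90%, even with no drop-out, and the protocol would have to say so.

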### 2.6. Outcome Measures

The primary evaluation outcome will be the change in the slope of Scr over 2 weeks. Posttreatment changes in BUN, eGFR, and urinary AKI biomarkers including urinary NGAL, IL-18, *γ*-GT, and TCM symptoms will be the secondary evaluation outcomes.

In addition to the secondary evaluation outcome, inflammatory indicators including TNF-*α* and IL-6 and oxidative stress indicators including heme oxygenase-1 (HO-1), malondialdehyde (MDA), and superoxide dismutase (SOD) will also be measured before and after treatment.

Safety outcomes and vital sign indicators (electrocardiogram, blood routine, urine routine, serum potassium, hemoglobin, etc.) will be recorded once before and 2 weeks after medication. Meanwhile, AEs will be closely observed, meticulously recorded, and properly handled by investigators throughout the study.

HCG: human chorionic gonadotropin; Scr: serum creatinine; BUN: blood urea nitrogen; eGFR: estimated glomerular filtration rate; TCM: traditional Chinese medicine; NGAL: neutrophil gelatinase-associated lipocalin: IL-18: interleukin-18; *γ*-GT: gamma-glutamyl transpeptidase; IL-6: interleukin-6; TNF-*α*: tumor necrosis factor-*α*; HO-1: heme oxygenase-1; MDA: malondialdehyde; SOD: superoxide dismutase.

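### Section 2.10 garbles the summary rule for non-normal data and names only an unadjusted t-test for normal data, which can be inefficient for skewed biomarkers

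*Protocol article*

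**What the plan says.** Section 2.10 (Statistical Analysis) gives one sentence on describing continuous data: "For non-normally distributed variables, mean ± standard deviation or median will be brought to describe continuous variables". It gives no separate rule for normally distributed variables and no measure of spread to accompany the median.

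On testing, the section says: "The secondary outcomes will be compared between two groups", "using the independent-samples Student's *t*-tests for normally distributed continuous data". Categorical data get a chi-square or Fisher test. No test or transformation is named for continuous data that are not normal. The section ends: "No additional analyses or interim analysis will be performed".

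Section 2.6 (Outcome Measures) sets the secondary outcomes: "Posttreatment changes in BUN, eGFR, and urinary AKI biomarkers including urinary NGAL, IL-18", together with γ-GT and TCM symptoms. It lists TNF-α, IL-6, HO-1, MDA and SOD as further indicators, in addition to the secondary outcomes. Table 3 schedules all these markers at baseline and at 2 weeks.

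**The concern.** The descriptive sentence is wrong as printed. Mean ± SD is the usual summary for roughly normal data, yet here it is offered for the non-normal case, and the normal case is not covered.

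The test rule then has a gap. The section expects non-normal variables, since it says how to describe them, but it gives a test only for normal ones. The outcomes most exposed are laboratory markers that cannot be negative and may vary by multiples, so right skew is plausible. If the one stated test is applied to raw changes in such markers, a few patients with high values dominate the variance. The baseline measurement enters only by subtraction, not as a covariate.

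At stake is how much the trial can learn about tubular injury, inflammation and oxidative stress, on which its rationale rests. A method chosen only once the distributions are seen would also be open to question.

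**Working it through.** **Inputs from the documents.** 54 randomised per group and 20% dropout (Section 2.9); two-sided testing at 0.05 (Section 2.10); changes from baseline to week 2 (Section 2.6, Table 3).

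**The plan's own figure first.** A three-group ANOVA F-test with means 160.39, 160.39 and 130.39 µmol/l, SD 44.43 and alpha 0.05 needs 43 per group for 90% power (power 0.9025). Then 43 / 0.8 = 53.75, rounded up to 54, which matches Section 2.9. So 43 evaluable per arm is used below.

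**Assumptions, none given in the documents.** Baseline and week-2 values are bivariate log-normal with the same log-SD s and correlation r. The true week-2 ratio between two arms is 0.6. Central case: s = 0.8, r = 0.5. Range: s = 0.5 to 1.0, r = 0.3 to 0.7.

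**Log-scale model with log baseline as covariate, central case.**
- Residual SD = s√(1 − r²) = 0.8 × √0.75 = 0.693.
- SE = 0.693 × √(2/43) = 0.149.
- Effect = |ln 0.6| = 0.511, so effect/SE = 3.42 and power is about 92%.

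**t-test on log change, central case.**
- SD = s√(2(1 − r)) = 0.8.
- SE = 0.8 × √(2/43) = 0.173.
- Effect/SE = 2.96 and power is about 83%.

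**t-test on raw change, central case.** Set the baseline median to 1.
- Mean = exp(s²/2) = exp(0.32) = 1.377.
- Variance V = exp(0.64) × (exp(0.64) − 1) = 1.700.
- Covariance C = exp(0.64) × (exp(0.32) − 1) = 0.715.
- If an arm's week-2 median is k times baseline, the mean change is (k − 1) × 1.377 and its variance is k²V + V − 2kC.
- Comparator flat (k = 1 and k = 0.6): difference = 0.4 × 1.377 = 0.551; variances 1.970 and 1.454; SE = √(3.424/43) = 0.282; ratio 1.95. That is just below the critical value of about 1.99, so power is near one half. Simulation gives 52%.
- Comparator also falling 40% (k = 0.6 and k = 0.36): difference = 0.24 × 1.377 = 0.331; SE 0.258; ratio 1.28. Simulation gives about 28% (27% to 29% over repeat runs). The log-scale results do not change.

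**Range, comparator flat (simulation, 10,000 trials per cell).**

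| log-SD | correlation | raw-change t-test | log-scale ANCOVA |
|---|---|---|---|
| 0.5 | 0.3 / 0.5 / 0.7 | 87% / 95% / 99% | about 100% in each |
| 0.8 | 0.3 / 0.5 / 0.7 | 42% / 52% / 71% | 86% / 92% / 98% |
| 1.0 | 0.3 / 0.5 / 0.7 | 26% / 31% / 45% | 69% / 77% / 90% |

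The loss is 1 to 12 points at log-SD 0.5, about 28 to 44 at 0.8 and about 43 to 46 at 1.0. With a comparator that also falls 40%, raw-change power over the same grid is about 15% to 77%.

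**Type I error.** With no difference between arms and no change over time, the raw-change t-test rejects in about 4% to 5% of trials across this grid.

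**Descriptive summary.** For a log-normal marker with median 100 and log-SD 1.0, the mean is 100 × exp(0.5) = 165 and the SD is 165 × √(e − 1) = 216. Mean minus SD is −51, an impossible concentration. This arises only if mean ± SD is chosen over the median, which the sentence permits but does not require.

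**The case against.** Much can be said for the plan.

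- The sentence offers the median as an alternative, so a reader who infers that mean ± SD is imposed on skewed data goes too far. A dropped clause is the likeliest explanation. This stands.
- A reader might infer that skewed markers have no valid analysis. The documents do not support that: at this group size the t-test holds its type I error. The question is efficiency.
- A reader might infer that real effects will probably be missed. That needs a degree of skew, a correlation and an effect size, none of which the documents give. At log-SD 0.5 with a flat comparator, the raw-change t-test keeps 87% to 99% power.
- The lowest power figures need the comparator arm to fall as well. That is plausible because every arm receives treatment, but it is an assumption.
- The loss is smaller if raw week-2 values rather than changes are compared. With the effect set for about 80% power on the log scale, the raw t-test has 75% at log-SD 0.5, 63% at 1.0 and 44% at 1.5. Section 2.6, however, specifies changes for the secondary outcomes.
- Part of the gap comes from baseline adjustment, not from the handling of skew: in the central case, log change gives 83% and log-scale ANCOVA 92%.
- An article may leave a fallback test to a full protocol or SAP. Its absence alone would not be a finding. The closing ban on additional analyses most naturally means subgroup or interim analyses, so it should not be read as forbidding such a test.
- TNF-α, IL-6, HO-1, MDA and SOD are listed beside the secondary outcomes, so the t-test sentence may not govern them.

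Two things remain: the descriptive sentence is wrong as printed, and the one test stated is a weaker choice than a method that uses baseline data already scheduled.

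**Conclusion.** The point holds as an error of wording plus an inefficient choice of method, at the level of secondary outcomes. Section 2.10 misassigns the summary for non-normal data, and its only test for continuous secondary outcomes is an unadjusted t-test for normal data.

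On raw changes in right-skewed markers, the cost in the central case is about 40 power points with a flat comparator (52% against 92%) and about 64 with a falling one (28% against 92%). Over the range examined with a flat comparator, power is about 26% to 99% against about 69% to 100%, so the loss runs from negligible at mild skew to about 46 points. All of this rests on assumed log-normal data, a ratio of 0.6 and 43 evaluable patients per arm. Bias and false-positive findings are not the issue. It should be corrected, but the primary analysis does not depend on it.

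**What to change.** 1. Replace the descriptive sentence: mean ± SD for approximately normal variables; median with quartiles, or geometric mean, for skewed ones.
2. Prespecify that urinary NGAL, IL-18 and γ-GT are analysed by a linear model on the log week-2 value, with arm (three levels) and log baseline as terms. Report geometric mean ratios with 95% CI for RG + CHF against each single-treatment arm. This also replaces the two-group wording, which does not fit a three-arm trial.
3. For consistency, apply the same model to TNF-α, IL-6, HO-1, MDA and SOD, and say that they are mechanism markers outside the secondary outcomes.

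A prespecified rank test would also close the gap for non-normal data, but it would not by itself adjust for baseline.

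Cost: wording only. Table 3 already schedules the baseline values, so no extra measurement is needed. The drawback is that results are ratios rather than absolute differences.

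### The primary test named in section 2.10 contains no arm term, so as written it does not test the between-arm hypothesis of section 2.9

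*Protocol article*

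**What the plan says.** Section 2.10 gives one sentence on the primary analysis: "The difference in Scr will be tested using the one-way ANOVA with repeated measures". It names no arm factor, group-by-time term, contrast or covariate, and it ends by ruling out further analyses.

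Section 2.6 defines the outcome: "The primary evaluation outcome will be the change in the slope of Scr over 2 weeks". Section 2.9 sizes the trial on a change in Scr: "The sample size will be calculated according to the primary outcome of baseline Scr change". The hypothesis in 2.9 is between arms: "Scr for CHF combing RG group would be significantly lower than the other two groups by more than 30" μmol/l. The same section gives a mean Scr of 160.39 μmol/l, says "the standard deviation was 44.43" μmol/l, and arrives at 54 per arm (162 in total) after 20% dropout.

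Table 3 schedules Scr at baseline and week 2 only, whereas section 2.5 speaks of weekly examinations.

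**The concern.** A one-way repeated-measures ANOVA has a single within-patient factor. With the two visits in Table 3 it is a paired t-test on all patients pooled, and treatment does not enter it. Its result can be significant when the arms do not differ, and non-significant when they do.

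If a mixed design was meant (arm between patients, time within), the sentence still does not say which term decides the trial. The group main effect and the group-by-time term answer different questions and have very different power. An omnibus three-arm test, on whichever term, also does not by itself show that RG+CHF beats each single-agent arm, which is what 2.9 claims. Leaving the choice open until outcome data are in hand would allow it to be made on the results.

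**Working it through.** **Inputs from the documents.** Difference 30 μmol/l, SD 44.43 μmol/l, power 0.90, α 0.05, 20% dropout, 54 per arm (section 2.9); two-sided testing (section 2.10); Scr at baseline and week 2 (Table 3).

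**Assumptions.** The SD is quoted beside a mean Scr level, so 44.43 is taken as the SD of Scr at each visit. The documents give no baseline-to-week-2 correlation r, so a range of 0.3 to 0.7 is used.

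**1. Reproducing the sample size.** Take a three-arm one-way between-group ANOVA with means 0, 0, −30. The grand mean is −10, so the sum of squared deviations is 10² + 10² + 20² = 600. The noncentrality is λ = n × 600 / 44.43². At n = 43, λ = 13.07, and power on (2, 126) df at α = 0.05 is 0.903; at n = 42 it is 0.895. So 43 per arm are needed, and 43/0.80 = 53.75, which rounds up to 54. This matches exactly.

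Two-arm comparisons do not match. One-sided 0.05 gives 38 per arm (48 with dropout), or 39 (49) with the t distribution. Two-sided 0.05 gives 47 (59), or 48 (60).

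**2. The test as named (time only, pooled).** With 129 completers the change has SD 44.43 × √(2(1 − r)), and the noncentrality is fall / (SD/√129). Suppose all arms fall by an assumed 10 μmol/l and do not differ:

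| r | SD of change | noncentrality | rejection rate |
|---|---|---|---|
| 0.3 | 52.57 | 2.16 | 57% |
| 0.5 | 44.43 | 2.56 | 72% |
| 0.7 | 34.42 | 3.30 | 91% |

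The reverse failure also occurs. Let RG+CHF have a true 30 μmol/l benefit, with the other two arms rising by 10 and RG+CHF falling by 20, so the mean change is (10 + 10 − 20)/3 = 0. In 2,000 simulated trials at each r, the time test rejected in about 4–5%.

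**3. The candidate arm terms.** Per pair of arms, 43 completers each, two-sided α 0.05, noncentral t with noncentrality δ / (SD × √(2/43)):

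- Group main effect: this averages baseline, where the arms are equal in expectation, with week 2. So δ = 30/2 = 15 and SD = 44.43 × √((1 + r)/2).
- Group-by-time: with two visits this is the comparison of change. δ = 30 and SD = 44.43 × √(2(1 − r)).
- ANCOVA on week-2 Scr with baseline as covariate: δ = 30 and SD = 44.43 × √(1 − r²).

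| r | Group main effect: SD, power | Group-by-time: SD, power | ANCOVA: SD, power |
|---|---|---|---|
| 0.3 | 35.82, 48% | 52.57, 74% | 42.38, 90% |
| 0.5 | 38.48, 43% | 44.43, 87% | 38.48, 95% |
| 0.7 | 40.96, 39% | 34.42, 98% | 31.73, 99% |

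**The case against.** The strongest reply is that the sentence is loose wording for a mixed design. The evidence is good: the hypothesis in 2.9 is between arms, the sample size reproduces from a between-arm ANOVA, and the secondary outcomes in 2.10 are compared between groups. On that reading the group-by-time term is valid. With two visits a patient's slope is the change divided by two weeks, so that term tests the outcome in 2.6 directly, and it is a more natural choice than the group main effect. This stands, and a reader should not conclude that the sponsor meant to compare only before with after. It does not supply the missing statement of which term is primary or which contrasts are tested. Nor is this a detail left to an analysis plan: the article names a specific test, and that test does not match its own hypothesis.

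Two stronger readings are tempting, and the documents support neither.

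- A reader might infer that the time test will be significant whatever the treatments do. That needs a recovery rate, and the documents give none; the Discussion in fact says that pre-existing CKD delays recovery after AKI. The rejection rates above depend on the assumed fall and on r.
- A reader might infer that leaving out baseline Scr biases the comparison. Under randomisation an unadjusted comparison of change is unbiased. Omitting the covariate costs only precision, and the absence of a covariate from a condensed article would not be a finding by itself.

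**Conclusion.** The point holds in this form: the primary test as written has no arm term, so it does not address the hypothesis that RG+CHF is lower than each of the other two arms by 30 μmol/l. An arm comparison was probably intended, but the text does not specify one.

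The choice of term moves power between roughly 40% and nearly 100%. At the unfavourable end (r = 0.3), group-by-time reaches 74% against the planned 90%, while ANCOVA keeps about 90%.

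These figures assume an SD of 44.43 μmol/l at both visits, 43 completers per arm, r between 0.3 and 0.7, and Scr at two visits only. With a week-1 Scr the group main effect would be diluted by a different amount. That the sample size came from a three-arm ANOVA is inferred from the exact match; section 2.9 names the software but not the procedure, and it describes the test as one-sided.

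**What to change.** Replace the sentence in 2.10 with a named between-arm analysis, for example: 'Week-2 Scr will be compared between arms by ANCOVA with arm (three levels) and baseline Scr. The primary estimates are the adjusted mean differences RG+CHF minus RG and RG+CHF minus CHF, with 95% confidence intervals.' With baseline in the model, using change from baseline as the response gives the same contrasts, so the outcome can still be presented as a change. If week-1 Scr is collected, use a mixed model with arm-by-visit and baseline Scr, and report the same two contrasts at week 2. First reconcile Table 3 with section 2.5 on whether it is collected.

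State whether both contrasts must succeed for the trial to be positive or, if either suffices, how they share alpha. Including centre is optional.

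The cost is small. No new data are needed, since baseline and week-2 Scr are already scheduled and SPSS fits the model. The one real decision is the rule for the two contrasts. Power should be rechecked against that rule, and the change should be made before any outcome data are examined by arm.
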